### Study outcomes

#### Primary study parameter

The primary study parameter is the number of overall postoperative complications within 30 days after surgery in the prehabilitation group and usual care group. Complications will be divided in surgical and non-surgical complications. Surgical complications will be scored as anastomotic leakage, perineal wound complication, rectal stump abscess, intra-abdominal abscess, fistula, sepsis, ileus, abdominal wound complication, intestinal necrosis, stoma complication, urological complication, bleeding, iatrogenic intestinal injury, or iatrogenic vascular injury. Non-surgical complications will be scored as cardiovascular, pulmonary, thromboembolic, renal, or neurological. Complications will be recorded and graded by using the Clavien-Dindo classification [75, 76]. Readmissions within 30 days will also be recorded.

#### Secondary study parameters

Secondary study parameters are 1) cardiorespiratory fitness, as indicated by the VAT, after the prehabilitation program in the intervention group just before surgery, 2) length of stay, 3) postoperative complications within 30 days after surgery in patients with a preoperative VAT ≥ 11 mL/kg/min and who will therefore not be included in the randomized controlled trial compared to patients in the prehabilitation or usual care group (for the prehabilitation group, we will use the post-prehabilitation CPET data), 4) the value of a limited geriatric assessment in this patient group to predict (in combination with VAT) postoperative complications, and 5) cost-effectiveness of prehabilitation.

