The primary objective of this randomized controlled trial is to evaluate the hypothesis that a three-week prehabilitation program (intervention group) will reduce the number of postoperative complications from 50% to 20% in patients with a preoperative VAT < 11 mL/kg/min who will undergo elective colorectal resection for colorectal cancer or dysplasia grade I, II, or III, when compared to usual care (control group).

The secondary objectives are 1) to observe whether changes in preoperative cardiorespiratory fitness occur in the intervention group (prehabilitation, single-arm study design), 2) to evaluate the effect of the prehabilitation program on length of stay, 3) to examine whether patients with a preoperative VAT ≥ 11 mL/kg/min, and who will therefore not be included in the randomized controlled trial, have fewer postoperative complications than patients in the prehabilitation or usual care group (for the prehabilitation group, we will use the post-prehabilitation CPET data), 4) to investigate the value of a limited geriatric assessment in this patient group to perform preoperative risk stratification, and 5) to evaluate the cost-effectiveness of prehabilitation in high-risk patients by performing a cost-effectiveness analysis.

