### Randomization

To analyze the effect of a three-week prehabilitation program on postoperative complications, patients with a VSAQ score ≤ 7 will be randomized in the intervention group (prehabilitation) or the control group (usual care) by using block-stratified randomization [37]. Randomization is stratified by disease and treatment type: 1) patients with colon cancer, 2) patients with rectal cancer who will receive one week of neoadjuvant radiotherapy, and 3) patients with rectal cancer who will receive five weeks of neoadjuvant chemoradiotherapy. The clinical research coordinator of the surgical department will be responsible for the randomization. Participants, care providers, and outcome assessors will not be blinded after randomization. However, the data analysts will be blinded to group allocation and are independent to the intervention. After randomization, all participants will perform a CPET for final inclusion, as merely patients with a VAT < 11 mL/kg/min can participate in the study.

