**Table 2 Tab2:** Content of the three-week peripheral resistance training program^a^

	Repetitions^b^	Duration	Intensity^c^
Week 1, session 1, 2, and 3	3 × 8 repetitions	20 min	70% of 1RM
Week 2, session 4, 5, and 6	3 × 8 repetitions	20 min	76% of 1RM
Week 3, session 7, 8, and 9	3 × 8 repetitions	20 min	82% of 1RM

^a^: Peripheral resistance training of the large muscle groups of the lower and upper extremities using open and closed kinetic chain exercises (without physical therapy equipment or machines): crouching by means of squat exercises (primary muscle group: quadriceps femoris; secondary muscle groups: gluteal muscles, hamstring muscles, and gastrocnemius muscle), pulling by means of pulley exercises (primary muscle groups: latissimus dorsi muscle and rhomboid muscles; secondary muscle groups: biceps brachii muscle, rotator cuff, and trapezius muscle), pushing by means of pulley exercises (primary muscle group: pectoral muscles; secondary muscle groups: shoulder muscles, triceps brachii muscle), and lifting by means of pulley exercises (primary muscle groups: trunk muscles and shoulder muscles; secondary muscle groups: quadriceps femoris, gluteal muscles, and trapezius muscle)

^b^: Rest intervals of 60-90 s between each set of repetitions

^c^: Based on the 10RM, the patient’s 1RM was determined using the Oddvar Holten diagram

Abbreviations: 1RM, one-repetition maximum; 10RM, ten-repetition maximum

Patients with colon cancer or dysplasia will participate in the prehabilitation program in the time between contemplation of surgery and the procedure, whereas patients with rectal cancer, in case neoadjuvant therapy is needed, will complete the physical exercise training program *prior to* radiotherapy (in case of neoadjuvant radiotherapy, 5 × 5 Gy) or in the twelve-week period *after* neoadjuvant chemoradiotherapy (training in the last three weeks before surgery).

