### Measurements

Both the prehabilitation group and usual care group will participate in a series of outcome measure assessments at baseline, seven days postoperatively, and 30 days postoperatively, whereas the prehabilitation group will participate in a series of outcome measure assessments after the three-week prehabilitation program as well (see Table 3).

**Table 3 Tab3:** Schedule of enrolment, interventions, and assessments

STUDY PERIOD	Enrolment	Allocation	Post-allocation					Follow-up	
			Pre-prehabilitation	Prehabilitation			Post-prehabilitation		
TIMEPOINT	-t_1_	0		Week 1	Week 2	Week 3		Day 7 post-surgery	Day 30 post-surgery
ENROLMENT:									
Eligibility screening	X								
VSAQ score (METs)	X								
Informed consent	X								
Allocation		X							
CPET	X								
INTERVENTIONS:									
Intervention group (prehabilitation program)									
Usual care group									
ASSESSMENTS:									
Baseline characteristics	X								
SNAQ score (0-5)	X								
VAT on CPET (mL/kg/min)			X				X^a^		
TUG test (s)			X				X^a^		
Muscle strength test			X				X^a^		
IADL			X						X
GDS 15			X						X
EORTC QLQ-C30			X						
GFI			X						X
Brief illness perception questionnaire			X				X^a^		
EQ-5D			X				X^a^		
Postoperative complications								X	X

^a^: Only for patients in the prehabilitation group

Abbreviations: CPET, cardiopulmonary exercise test; EORTC QLQ-C30, quality of life questionnaire of the European organisation for research and treatment of cancer; EQ-5D, EuroQol 5D; GDS 15, geriatric depression scale 15; GFI, Groningen frailty indicator; IADL, instrumental activities of daily living; MET, metabolic equivalent of task; SNAQ, short nutritional assessment questionnaire; TUG, timed up-and-go; VAT, ventilatory anaerobic threshold; VSAQ, veterans-specific activity questionnaire

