#### Cardiopulmonary exercise test

A CPET will be used at baseline to assess cardiorespiratory fitness, as indicated by the VAT, in order to select and thereupon advice/invite eligible patients to participate in the study. For patients in the prehabilitation group, a second CPET will be used to investigate the effect of the prehabilitation program on cardiorespiratory fitness (single-arm study design). Patients free from any absolute and/or relative exclusion criteria, as stated by the American Thoracic Society and American College of Chest Physicians position statement [42], will be able to perform the CPET. The following standardized pre-test instructions will be given to the patients: 1) consume the last (light) meal at least 2 hours before exercise testing, 2) adhere to usual use of medication, and 3) wear comfortable sporting clothes and shoes. The CPET will be performed under controlled conditions at the lung function department of both hospitals, using a calibrated electronically braked cycle ergometer (Ergoline, Ergoselect 100, Bitz, Germany at Medisch Spectrum Twente and Lode Excalibur Sport, Lode BV, Groningen, the Netherlands at Ziekenhuisgroep Twente). Seat height will be adjusted to the patient’s leg length. During the CPET, patients breathe through a facemask (Hans Rudolph, Kansas City, MO, USA) connected to a Triple V volume transducer to perform breath-by-breath measurements of oxygen uptake, carbon dioxide production, respiratory flow, and volume parameters (Oxycon Pro, Jaeger, Hoechberg, Germany). In both hospitals the same respiratory gas analysis system will be used. Before each CPET at the Medisch Spectrum Twente and each morning at the Ziekenhuisgroep Twente, flow-volume calibration (three-liter syringe) and gas calibration (ambient air and a gas mixture of 16% oxygen and 5% carbon dioxide) will be performed, and ambient conditions are set. Twelve-lead electrocardiography will be used to continuously monitor heart rate during the test. Blood pressure (SunTech Tango+, SunTech Medical, Inc., Marrisville, NC, USA) will be automatically measured every three minutes to be aware of extreme hypertension or to detect hypotension. Oxygen saturation (Nonin 9600, Nonin Medical, Inc., Plymouth, MN, USA) is continuously recorded during the test by finger pulse oximetry.

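### For rectal cancer patients given neoadjuvant therapy, the timing of the two CPETs does not match how the VAT parameter is defined and read

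*Protocol article*

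**What the plan says.** All references are to the Protocol article.

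- **What is asked.** Secondary objective 1 (Background) is "to observe whether changes in preoperative cardiorespiratory fitness occur in the intervention group (prehabilitation, single-arm study design"). The matching parameter (Secondary study parameters) is "cardiorespiratory fitness, as indicated by the VAT, after the prehabilitation program in the intervention group just before surgery". Neither is divided by disease or treatment.
- **How the change is read.** Under Cardiopulmonary exercise test, "a second CPET will be used to investigate the effect of the prehabilitation program on cardiorespiratory fitness (single-arm study design").
- **When the second test falls.** Under Measurements, "the prehabilitation group will participate in a series of outcome measure assessments after the three-week prehabilitation program as well". Table 3 agrees: the second VAT sits in the Post-prehabilitation column. It is tied to the end of training, not to the date of surgery.
- **When training falls.** Under Prehabilitation program, patients having 5 × 5 Gy "will complete the physical exercise training program *prior to* radiotherapy". Those having chemoradiotherapy train after it: "neoadjuvant chemoradiotherapy (training in the last three weeks before surgery"). The Fig. 1 legend gives weeks 10-12. Colon cancer and dysplasia patients train in the interval before their operation, with no neoadjuvant treatment described.
- **When the first test falls.** Under Randomization, one stratum is "patients with rectal cancer who will receive five weeks of neoadjuvant chemoradiotherapy", and "After randomization, all participants will perform a CPET for final inclusion". Recruitment calls this CPET part of the standard work-up.
- **Second use.** Secondary parameter 3 also uses the post-programme CPET for the prehabilitation group.

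**The concern.** A before-after change in one arm can be credited to the programme only if little else happens between the two tests. A value can be called immediately preoperative only if little happens between that test and the operation. Neoadjuvant therapy can break either condition, and it does so differently in the two rectal strata.

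What is at stake is the meaning of secondary objective 1. If all intervention patients are summarised together, the VAT change combines a clean training change, a training change measured before radiotherapy, and possibly a change spanning chemoradiotherapy, recovery and training. A reader could not tell which of these drives the result. The short-course value also enters secondary parameter 3 as if it described fitness at surgery.

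**Working it through.** The document gives no figure for the VAT parameter, so there is none to reproduce. Its only derived figure, 39 per group for complications, does reproduce (two-sided, alpha 0.0492, power 0.80, no continuity correction; power at 39 is 0.803). It does not depend on CPET timing.

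**Step 1. Order of events by group, from the sections cited above.**

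| Group | Order as written | Neoadjuvant treatment between CPETs? | CPET 2 shortly before surgery? |
|---|---|---|---|
| Colon, dysplasia, rectal without neoadjuvant therapy | CPET 1, training, CPET 2, surgery | No | Can be |
| Rectal, 5 × 5 Gy | CPET 1, training, CPET 2, radiotherapy, surgery | No | No |
| Rectal, chemoradiotherapy, early baseline | CPET 1, chemoradiotherapy, wait, training, CPET 2, surgery | Yes | Yes |
| Rectal, chemoradiotherapy, late baseline | Chemoradiotherapy, wait, CPET 1, training, CPET 2, surgery | No | Yes |

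The short-course row follows directly from the text. The interval from radiotherapy to surgery is not stated.

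**Step 2. Which chemoradiotherapy row applies?**

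For an early baseline:
- The stratum is defined by treatment still to come.
- The CPET is called work-up and decides final inclusion.
- Table 3 marks CPET in the Enrolment column.
- The same test decides inclusion in usual care, where there is no training start to tie it to.
- A late baseline would leave randomised patients unconfirmed for about 14 weeks.

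For a late baseline:
- Table 3 has a separate row for VAT on CPET, marked under Pre-prehabilitation, after allocation.
- Recruitment says patients are told the CPET date a few days later, not that the test is done then.

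The early reading fits more of the text, but no sentence settles it.

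**Step 3. Intervals under the early reading.** Inputs are five weeks of chemoradiotherapy (Randomization) and training in weeks 10-12 afterwards (Fig. 1 legend).
- Baseline CPET to start of training: 5 + 9 = 14 weeks at least.
- Between CPETs: 5 + 12 = about 17 weeks.

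Under the late reading, no treatment lies between the tests.

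**Step 4. Does the protocol's own defence cover this?** The Discussion supports the missing control CPET with a hepatic-resection study that found no significant change in its controls over a four-week wait. Four weeks without treatment says nothing about 17 weeks that include chemoradiotherapy.

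**Step 5. Size, as illustration only.** If a share *s* of the arm had chemoradiotherapy and lost *d* mL/kg/min before training, a pooled mean change would be too low by *s × d*. The document gives neither quantity and does not say that VAT falls. With *s* = 5-30% and *d* = 0.5-2.0 (both assumed), the shift runs from 0.05 × 0.5 = 0.025 to 0.30 × 2.0 = 0.60 mL/kg/min. For scale, the cited programme aimed at a gain of 1.5 mL/kg/min (Background). Under the late reading the shift is zero.

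**The case against.** The other side has four good arguments.

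- **No group fails on both counts.** A reader might infer that the VAT result is neither a training change nor preoperative fitness, or that two of the three strata cannot answer objective 1. The text does not support that. Colon and dysplasia patients can satisfy both descriptions, short-course patients give a valid training change, and chemoradiotherapy patients are tested close to surgery.
- **The chemoradiotherapy part is not established.** Table 3's Pre-prehabilitation VAT row permits a baseline just before training. This stands: the 17 weeks are conditional.
- **Pooling is not stated.** The objective and parameter simply do not mention strata, and a split may be specified in an analysis plan that is not shown. This also stands, so the absence of a split is not itself the fault. What remains is a parameter definition and a schedule that this document states and that do not agree.
- **The consequences are limited.** Objective 1 is observational, in one arm and secondary, and the Discussion admits that controls have no second CPET. A reader might extend the point to the primary endpoint because the eligibility VAT could predate treatment. The documents do not support that: the eligibility test applies alike to both arms, and the complication comparison does not use the second CPET.

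The objection does not remove the short-course conflict, which is plain in the text. Nor does the Discussion's limitations paragraph mention neoadjuvant therapy between the tests.

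**Conclusion.** The point holds in two parts of different strength.

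1. **Short-course stratum: established.** Radiotherapy lies between the second CPET and surgery, so the definition of secondary parameter 1 is wrong for these patients, and the same value is carried into secondary parameter 3. The training change itself is sound.
2. **Chemoradiotherapy stratum: probable.** If the baseline CPET is at work-up, about 17 weeks separate the tests, and the change is probably not a pure effect of the programme. This rests on the early reading of the text; Table 3 leaves the other reading open.

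An unsplit single-arm result would mix these quantities. How far it would be shifted cannot be derived, because stratum shares and any VAT change over treatment are not given; the range under working is illustration, not a finding. The primary comparison and the sample size are unaffected. The correction should be made because it costs almost nothing and makes objective 1 interpretable.

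**What to change.** 1. Report VAT change by the existing randomisation strata. Dysplasia and rectal cancer without neoadjuvant therapy are not named in those strata, so state where they are counted.
2. Base the main training-change estimate on patients with no neoadjuvant treatment between the two CPETs: colon, dysplasia, rectal without neoadjuvant therapy, and short-course. Show the chemoradiotherapy stratum separately.
3. Label the short-course second VAT *end of programme, before radiotherapy*, in secondary parameter 1 and wherever it is used in secondary parameter 3.
4. Record the dates of both CPETs and of surgery, and report the intervals.
5. Have the sponsor reconcile Recruitment, Randomization, Prehabilitation program and both CPET entries in Table 3 on when the baseline test falls for chemoradiotherapy patients. Table 1 expresses training intensity relative to a CPET, so the answer also determines which test is meant there. No schedule is proposed here.

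The cost is wording, date fields and a stratified table, with no extra tests. The downside is that the main VAT-change estimate rests on somewhat fewer patients than the full intervention arm.

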The literature shows that high-risk patients (those patients with a higher likelihood of postoperative complications), who participated in a physical exercise training program prior to elective surgery (prehabilitation), improved their cardiorespiratory fitness [23–25], which has led to the hypothesis that postoperative complications can be reduced by prehabilitation [23, 25–27]. Dunne et al. [28] designed a four-week high-intensity interval training program based on the work rate at the VAT for patients prior to hepatic resection. Their aim was to assess feasibility and to improve the preoperative VAT by 1.5 mL/kg/min (a 10% increase). They found their program to be feasible in sedentary healthy volunteers, resulting in a > 10% improvement in cardiorespiratory fitness (VAT). Using preoperative risk stratification, a 10% improvement in cardiorespiratory fitness in patients undergoing hepatic resection would shift 30% of the high-risk patient group to a low-risk patient group [28].

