### Participants

To be eligible to participate in this study, a patient must meet all of the following inclusion criteria: 1) ≥ 60 years, 2) colorectal cancer or premalignant colorectal lesions (dysplasia grade I, II, or III) requiring colorectal resection, 3) undergoing elective colorectal resection at Medisch Spectrum Twente, Enschede, or at Ziekenhuisgroep Twente, Almelo, 4) having a life expectancy of more than 6 months as estimated by the surgeon, 5) has given informed consent to participate in this study, 6) a metabolic equivalents of task (MET) score ≤ 7 on the veterans-specific activity questionnaire (VSAQ), 7) able to perform a CPET, 8) a VAT < 11 mL/kg/min as measured at the baseline CPET, and 9) willing to perform prehabilitation at a community physical therapy practice in the adherence area of both hospitals. All patients not meeting these criteria will not be considered for inclusion. Participants can leave the study at any time for any reason if they wish to do so, without any consequences. The investigator can decide to withdraw a participant from the study for urgent medical reasons.

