During the CPET, absolute values at peak exercise are calculated as the average value over the last 30 seconds prior to termination of the test. Peak heart rate is defined as the highest heart rate achieved during the CPET. Cardiorespiratory fitness will be assessed by determining the VAT, by evaluating the peak oxygen uptake in case the patient performed a maximal effort, and by calculating the oxygen uptake efficiency slope [44]. The VAT will be detected by using the V-slope method, which is based on analyzing the slopes of oxygen uptake and carbon dioxide production. The VAT can be determined by using computerized regression analysis of these slopes. The point at which the linear slope of the relation between the carbon dioxide production and oxygen uptake changes, is called the VAT [45]. When the V-slope is expected to be unreliable, the ventilatory equivalents will be used to determine the VAT [46]. In this ventilatory equivalents method, the VAT will be defined as the point at which the ventilatory equivalent for oxygen and the partial end-tidal oxygen tension reached a minimum and thereafter began to rise in a consistent manner, coinciding with an unchanged ventilatory equivalent for carbon dioxide and partial end-tidal carbon dioxide tension [42]. The inter-observer variability in a preoperatively measured VAT has been reported to be acceptable for experienced clinicians [7], and DeCato et al. [47] recently reported short-term repeatability for CPET parameters in healthy participants in a similar test protocol, and they found no evidence for a learning effect and no significant differences in variability related to sex, age, fitness level, and diurnal factors.

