#### Other study parameters

Preoperative factors that could be associated with postoperative complications will be recorded, these include: age, sex, body height, body mass, body mass index, nutritional status, smoking status, location and type of the tumor, presence or absence of metastases, CPET parameters other than the VAT, WHO performance score, ASA score [77], Charlson comorbidity index [59], type of surgical resection, muscle strength, and the TUG test.

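### The single-arm change in VAT can mix detection methods, body masses and unmasked readings, so part of an apparent gain may not be a gain in fitness

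*Protocol article*

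**What the plan says.** All places are in the protocol article.

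- **Outcome.** Secondary study parameters, item 1: "cardiorespiratory fitness, as indicated by the VAT, after the prehabilitation program in the intervention group just before surgery".
- **Design.** In the section on the cardiopulmonary exercise test (CPET), for the prehabilitation group "a second CPET will be used to investigate the effect of the prehabilitation program on cardiorespiratory fitness (single-arm study design"). Table 3 marks the post-programme VAT as applying to that group only. The Discussion lists the lack of a second test in usual care as the first limitation.
- **Detection method.** The same CPET section makes V-slope the first choice: "The VAT will be detected by using the V-slope method, which is based on analyzing the slopes of oxygen uptake and carbon dioxide production". It then adds a fallback: "When the V-slope is expected to be unreliable, the ventilatory equivalents will be used to determine the VAT". Nothing in the text ties a patient's two tests to one method.
- **Scale.** Table 3 lists the measure as "VAT on CPET (mL/kg/min"). Eligibility uses the same scale: "a VAT < 11 mL/kg/min as measured at the baseline CPET".
- **Body mass.** Other study parameters lists "age, sex, body height, body mass, body mass index, nutritional status, smoking status" among the preoperative factors. The article does not say whether patients are weighed again at the second test, or which mass is then the divisor.
- **Blinding.** The Randomization section leaves outcome assessors unblinded; only the data analysts are blinded.

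**The concern.** A fallback rule that works test by test is adequate for one eligibility reading. It is less suited to a difference between two readings in the same patient, because whatever differs between the tests besides fitness goes into that difference. Three things can differ:

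1. **Method.** One reading may come from V-slope and the other from ventilatory equivalents. The trigger for the fallback is a judgement.
2. **Body mass.** A per-kg value rises when mass falls, even if oxygen uptake at the threshold is unchanged. This is a colorectal cancer population that is screened for malnutrition (Nutritional status).
3. **Reading.** Every second CPET follows training, so an unmasked reader who chooses the method and break point knows which test it is. Blinding the data analysts does not help, because the reading is made before their work begins.

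In a two-arm comparison of change, shifts common to both arms would cancel. Here there is no second reading in usual care. At stake is how the VAT change is interpreted. Secondary parameter 3 also draws on the post-prehabilitation CPET data, so it may be touched as well.

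**Working it through.** **Yardstick.** The article states no expected VAT gain for this trial. The nearest figure is the aim of the cited four-week programme before hepatic resection (Background), to "improve the preoperative VAT by 1.5 mL/kg/min (a 10% increase"). That implies a starting VAT of 1.5 / 0.10 = 15 mL/kg/min. Here the baseline is below 11, so a 10% gain is below 0.10 × 11 = 1.1 mL/kg/min. At an illustrative baseline of 10 it is 1.0 mL/kg/min.

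**Body mass (losses are assumptions).** Hold oxygen uptake at VAT constant and let mass fall by a fraction w. Per-kg VAT becomes VAT / (1 − w), a relative rise of w / (1 − w). Its share of a 10% gain is [w / (1 − w)] / 0.10, whatever the baseline.

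| Mass loss | VAT from 10 mL/kg/min | Rise | Share of a 10% gain |
|---|---|---|---|
| 1% | 10 / 0.99 = 10.10 | 0.10 | 10% |
| 2% | 10 / 0.98 = 10.20 | 0.20 | 20% |
| 3% | 10 / 0.97 = 10.31 | 0.31 | 31% |
| 5% | 10 / 0.95 = 10.53 | 0.53 | 53% |

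Half of a 10% gain needs a mean loss of 1 − 1/1.05 = 4.8%; the whole of it needs 1 − 1/1.10 = 9.1%. A gain in mass has the opposite sign.

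**Method switching (difference and frequency are assumptions).** If the methods differ by b, the shift in the group mean is b × (net share of patients switching in one direction). With b from 0.25 to 1.0 mL/kg/min and a net share of 10% to 30%, the shift runs from 0.25 × 0.10 = 0.025 to 1.0 × 0.30 = 0.30 mL/kg/min, or 2.5% to 30% of a 10% gain at VAT 10. If switches balance, the mean shift is 0 and only the variance grows.

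**Break-point placement (shift, 10 mL/min oxygen uptake per W and 80 kg are assumptions).** The work rate rises by 5 to 15 W each minute (CPET section). Placing the break point later by t minutes adds rate × t × 10 / 80 mL/kg/min:

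- 5 W/min, 15 s: 5 × 0.25 × 10 / 80 = 0.16
- 10 W/min, 15 s: 10 × 0.25 × 10 / 80 = 0.31
- 15 W/min, 30 s: 15 × 0.50 × 10 / 80 = 0.94

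These are effects on one reading. They move the group mean only if the placement drifts in the same direction across patients.

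**Threshold.** A patient at 10.7 mL/kg/min who loses 3% of body mass reads 10.7 / 0.97 = 11.03, above the cut-off of 11, with no change in oxygen uptake.

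**Sample size.** The stated 39 per group (50% versus 20%, alpha 0.0492, power 0.80) is reproduced by the two-sided comparison of two proportions without continuity correction. It rests on complications, so nothing here changes it.

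**The case against.** A reader might infer that much of the expected gain could be artefact. The documents do not support that. They give no weight-change figure, no difference between the methods and no rate of fallback. Assumed losses of 1-3% reach only 10-31% of a 10% gain, and the programme lasts three weeks. The 0.94 mL/kg/min figure combines the steepest work-rate step with a 30-second shift, in a population selected for low fitness. If baseline mass is already the divisor at both tests, the mass artefact is zero.

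A reader might also infer that a weak first test favours the fallback, so that switching runs one way. No passage says so. The Background calls VAT submaximal and little affected by effort. The CPET section cites acceptable inter-observer variability and, in healthy participants, no learning effect. These points weaken any claim of direction, but they do not address a method switch, a mass change or an unmasked reader.

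Nor is VAT the only evidence on fitness. The CPET section also assesses peak oxygen uptake (when effort is maximal) and the oxygen uptake efficiency slope, neither of which needs a VAT break point. Strength and the timed up-and-go test are repeated too.

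Finally, the article condenses a protocol that is not shown and that may hold a same-method or weighing rule, and the single-arm limitation is disclosed. Both are fair and keep the point modest. What remains is that the rule and scale as stated are a loose fit for a paired change, and disclosing the missing control test does not tighten them.

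**Conclusion.** The point holds as a cheap improvement to one secondary analysis. As written, the plan allows a method switch, a loss of body mass or a drift in the break point to account for part of an apparent VAT gain, with no control change to subtract. Size and direction are unknown from the documents. The mass effect is exact arithmetic once a loss is assumed: 1-3% at VAT 10 gives 0.10-0.31 mL/kg/min, about 10-31% of a 10% gain, provided current mass is the divisor at each test. The method and reading effects rest wholly on assumed values, and they bias the mean only if they run predominantly one way.

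One point cannot be settled from the text. For patients who have chemoradiotherapy, it is unclear whether the baseline CPET comes before or after that treatment. If it comes before, the interval between the tests is much longer than three weeks, with more room for mass to change. The use of post-prehabilitation data in secondary parameter 3 is likewise not specified enough to size any effect there.

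**What to change.** For the before-after VAT change only:

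1. Use one detection method for both tests of a patient: V-slope for both, or ventilatory equivalents for both if V-slope is unreliable in either. This removes the method artefact.
2. Report the change in oxygen uptake at VAT in mL/min, or per kg of baseline mass, alongside mL/kg/min. This gives a result free of the mass artefact. Keep mL/kg/min as the eligibility scale.
3. Where the tests are stored, have the existing reader determine both tests of each patient with date and order masked. At 43 patients that is at most 43 × 2 = 86 readings.

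The text change is about one sentence each in the CPET section and under Secondary study parameters. No new test, extra reader or change in sample size is needed. The costs are the re-reading, the need to know body mass at the second test if only per-kg values were kept, and the possible loss from this analysis of a few patients with no common reliable method. The number lost should be reported.
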